# Assessing the Noninferiority of a Rhythm and Language Training Serious Game Combined With Speech Therapy Versus Speech Therapy Care for Children With Dyslexia: Protocol for an Investigator-Blinded Randomized Controlled Trial

**DOI:** 10.2196/71326

**Published:** 2025-04-03

**Keywords:** dyslexia, serious game, rhythm, randomized controlled trial, non-inferiority protocol

## Abstract

**Background:**

Specific learning disorder (SLD) of reading skills impacts approximately 7% of children. Speech and reading therapy is currently the gold-standard intervention for improving children’s reading abilities. However, intensive interventions are difficult to implement. Recently, numerous studies have investigated the interest of game- and home-based training approaches to enhance children’s motivation and facilitate intensive learning activities in home settings. The serious game Poppins Clinical integrates rhythm and specific written language exercises to improve reading skills in children with SLD.

**Objective:**

This study aimed to assess the noninferiority of Poppins Clinical combined with a reading specialist session once every 2 weeks versus a reading specialist session every week, on the reading skills of children with SLD.

**Methods:**

A total of 306 children with dyslexia will be recruited for this study and randomly assigned to either the experimental or control group. Children in the experimental group will use the serious game Poppins Clinical at home for 20 minutes, 5 days a week, and attend 1 reading therapy session every 2 weeks. The control group will participate in one reading therapy session per week. Poppins Clinical combines rhythm and language exercises integrated into an engaging game designed to maintain user motivation. We will use a noninferiority paradigm to assess the clinical impact of both interventions in terms of reading accuracy, reading speed, and reading comprehension. We will also investigate the evolution of phonological and visual-attentional skills. However, we will explore the impact of the protocol on parental stress and children’s perception of their difficulties. Finally, we will also assess the cost of medical care and the impact of introducing the serious game Poppins Clinical on reading therapy. To facilitate recruitment and ensure the representativeness of our sample, the evaluation of the children will be conducted via videoconference using standardized tests that have been adapted for videoconference administration.

**Results:**

Patient recruitment is expected to start in December 2024, with study completion by the end of August 2025.

**Conclusions:**

This study should allow us to assess the interest in using the serious game Poppins Clinical in addition to reading therapy to improve reading abilities in children with SLD.

**Trial Registration:**

ClinicalTrials.gov NCT06592911; https://clinicaltrials.gov/study/NCT06592911

**International Registered Report Identifier (IRRID):**

DERR1-10.2196/71326

## Introduction

Specific learning disorder (SLD) with impairment in reading is a type of SLD classified as a neurodevelopmental disorder according to the *DSM-5* (*Diagnostic and Statistical Manual of Mental Disorders* [Fifth Edition]). The disorder affects reading and spelling abilities as well as related language processing skills such as phonological skills or auditory attention, despite adequate instruction, and in the absence of general cognitive or sensory deficits [1]. Yang et al [2] estimated the prevalence of SLD at around 7% in primary school children, suggesting that this disorder represents a considerable public health challenge.

It is now well established that SLD is caused by problems at the level of phonological representation, characterized by difficulty in accessing or manipulating speech sounds [1]. Recently, several studies revealed a deficit in the temporal processing of speech, which could explain the phonological deficit observed in people with SLD [3-5]. This deficit does not seem to be specific to the processing of speech but applies to the temporal treatment of the auditory signal in general. Effectively, the ability to process rhythm in music is linked with the processing of linguistic prosody in children and adults. However, musical rhythm perception skills predict metaphonological and reading skills [6,7]. People with SLD have difficulty estimating changes in the amplitude of the sound envelope over time [8], processing short durations [5], preattentive processing of vowel duration and voicing establishment [9], and also processing rhythmic information. This is particularly the case in the synchronization of simple rhythmic sequences, such as a metronome, or complex ones, such as music, where people with SLD are more variable [4,10,11]. They also have difficulty identifying whether a sequence is regular or not [11,12]. Rhythm perception and production skills even predict reading skills in children with SLD with reading deficits [12]. Regarding the strong link between rhythm perception and reading skills, several studies tried to improve reading skills in children with SLD through musical training [13]. Among them, some studies specifically focused on the training of rhythm skills. As an example, Flaugnacco et al [12] compared the impact of rhythm training to art training on phonological and reading skills in children with SLD. In this randomized controlled trial including 46 children with SLD, children receiving the rhythm training significantly improved their phonological and reading skills, more than the group of children receiving art training.

The “Recommendations for good practice in the assessment, prevention, and treatment of written language disorders in children and adults” by the Collège Français d’Orthophonie [14] describe three different modes of intervention for patients affected by SLD: (1) corrective treatment targets underlying cognitive deficits (eg, phonological or visual-attentional deficits) and various processes involved in identifying written words (eg, graphophonological conversion, phonological decoding, orthographic memory, and orthographic recoding), (2) adaptive treatment aims to reinforce the reader’s natural compensatory strategies (eg, lexical orthographic memory formation), and (3) compensatory treatment seeks to reduce written language disorders by replacing deficient cognitive functions (eg, using digital aids). These modes of intervention are not mutually exclusive and should be combined or alternated according to a treatment plan defined for each patient. However, when possible, corrective treatment should be the first option applied to a patient. For the intervention to be effective, it must be intensive (5 times a week). Achieving this intensity is not feasible in conventional in-person speech and reading therapy, where therapists are generally limited to scheduling 1-2 sessions per week [15]. Therefore, learning activities must also be carried out at home to ensure sufficient training frequency.

In recent years, there has been growing interest in digital technologies and game-based assessment, training, and rehabilitation methods for neurodevelopmental disorders [16,17]. As defined by Mayer [18], serious games have the motivational and playful characteristics of games, but their main objective is to achieve a measurable change in the player’s skills. The playful nature of these games leads to increased interest and attention from the player, which in turn encourages greater effort [18,19]. However, the digital tool appears to be a preferred learning tool for school-age children [20]. Digital tools also enable the multimodal, sequential, and simultaneous presentation of information, allowing the player to interact with the device in various ways [21]. A recent review of serious games for people with SLD supports their effectiveness in developing reading abilities, particularly those targeting sound and letter association and action video games [22]. In addition, serious gaming could be an ideal medium for training rhythmic skills, as rhythmic synchronization is one of the easiest musical skills to isolate [23]. Furthermore, serious games enable the use of an active musical framework in which body movements, emotions, and intentionality influence each other, maximizing the demands on the audio-motor loop and enhancing anticipatory and predictive processing [24]. Indeed, serious games provide an interesting medium to combine musical training with grapheme-phoneme correspondence, as recommended by recent guidelines [14]. The serious game Poppins Clinical was created to combine written language exercises and rhythm training, allowing children with SLD to practice at home and improve their reading skills. The rhythm training part is the most original component and has been used with children with neurodevelopmental disorders, showing improvement in rhythm skills within the game [25]. A randomized placebo-controlled trial involving 154 children with SLD tested the rhythm training part or a placebo game for 2 months [26]. The results showed improvement in reading accuracy and speed, supporting the efficacy of Poppins Clinical to improve reading skills in children with SLD. Written language exercises have been added to the rhythm training to match the most recent recommendations [14].

The use of new technologies, including serious games, raises several questions, notably regarding how these new technologies are used in the current health system [27]. Specifically, cost-effectiveness data is lacking. It is crucial to evaluate the impact of a technology compared with its cost [27]. In addition, the impact of a new treatment must also take into account other variables such as treatment adherence or safety. To assess these points, a number of trials use a noninferiority paradigm [28,29]. The objective of these trials is to evaluate if a new treatment can be considered not worse than the gold-standard treatment by an acceptably small amount, with a given degree of confidence [30]. In this type of trial, defining the noninferiority margin is crucial [30]. This margin represents the threshold below which any difference in efficacy is considered clinically acceptable. Elicited health costs can be considered to evaluate the gain of the treatment. These costs may be divided into three types of costs: direct costs related to resources used, indirect costs related to productivity loss, and intangible costs as costs related to pain and endurance [31]. As an example, Schmidt et al [32] identified 31 subcategories of “out-of-pocket” costs such as transportation, insurance, or technology-related costs, that could be considered when looking at health expenditures.

The objective of this paper is to present the methodology of a randomized controlled trial aimed at comparing the effectiveness of Poppins Clinical combined with one reading therapy session every 2 weeks to one reading therapy session per week, on the reading skills of children with SLD, using a noninferiority paradigm. Safety, treatment adherence, and cost will also be considered.

## Methods

### Study Design and Objectives

This study is an interventional, multicenter, noninferiority randomized trial with two arms. The main objective is to evaluate the noninferiority of Poppins Clinical combined with one reading therapy session every 2 weeks (experimental arm) compared with one reading therapy session every week (control arm) on the reading accuracy (the primary end point) of children with SLD and reading impairment.

Secondary objectives include comparing the experimental group to the control group in terms of safety, reading speed, reading skills, phonological awareness, parental stress, parent quality of life, and text comprehension (secondary end points). Costs related to medical care and therapy between the experimental and control groups are also investigated. This protocol follows SPIRIT (Standard Protocol Items: Recommendations for Interventional Trials) guidelines (checklist provided in Multimedia Appendix 1).

### Study Population

The study will include 306 participants. The justification for the sample size is given below in the *Statistical Justification of the Sample Size* section.

Inclusion criteria require participants to have a confirmed diagnosis of SLD with a reading deficit, as defined by a speech-language assessment. This diagnosis must align with the *DSM-5-TR* (*DSM-5*, Text Revision) definitions, with reading and/or transcription test scores showing an SD of at least –1.4 or below the 20th percentile, or –2 SD and below the 10th percentile on two such tests. Eligible participants will be children aged 7-11 years, enrolled from CE1 to CM2, who have been receiving reading therapy once a week for less than 2 years. Other criteria include fluency in French or bilingualism in French at home, at least 3 years of schooling in France, and access to a tablet or smartphone at home. In addition, participants must be affiliated with the French National Insurance system, and both the child and their legal guardians must provide informed consent and agree to follow the study protocol. Only one child per family will be enrolled.

Exclusion criteria will exclude individuals who have previously used Poppins Clinical or its earlier version, Mila-Learn (Poppins). Children with unstabilized chronic illnesses, autism spectrum disorders, or documented intellectual disabilities will not be eligible. Participants with vision or hearing impairments that would prevent the use of a tablet or smartphone, as well as those engaged in other interventional studies that may affect the trial’s outcomes, will also be excluded.

### Study Procedure

First, participants will be informed about the study either by their therapists or via web-based social media platforms. Two clinical sites in Paris and Poitiers, France, will be in charge of the screening and recruitment. Potentially eligible children and their legal representatives will receive study information during an informational visit. If interested, legal representatives will be asked to sign the informed consent form. Speech and reading therapists working with the participants will also be officially informed about the study, and their consent will be collected. The study investigator will then verify whether the participant meets the study criteria and determine their eligibility during an inclusion visit, which can be conducted either on-site or via videoconference. During this visit, verbal assent will also be obtained from the child. Following this, a baseline evaluation (T1) will be conducted by a speech therapist from the clinical site via videoconference, and questionnaires will be provided to both the patients and their legal guardians. These assessments will be performed under the same conditions as renewal evaluations, using standardized tests that have been adapted for videoconference administration.

Patients will then be randomized into one of two groups: the experimental arm or the control arm. Randomization will be carried out by the Contract Research Organization (CRO) using blocks of size six to maintain a 1:1 ratio, with stratification based on the participant’s schooling level.

Patients assigned to the experimental arm will undergo 12 weeks of reading therapy, with one session every two weeks. In addition, they will use the medical device Poppins Clinical for 20 minutes per day, 5 days a week, over 12 weeks. The Poppins Clinical device is provided free of charge to families during the three-month training period. Each family must create an account in the game using a specially generated link designed to track study participants. The patient’s playtime is recorded by Poppins Clinical—the time spent on each exercise is tracked, enabling the app to monitor the children’s daily playtime. The patient will receive a notification on their tablet every Monday encouraging them to play, and another on Saturday to motivate them to reach the playtime goal. If they have not played during the week, the child will receive an additional notification the following Wednesday to encourage them to play. The first day of training in the Poppins Clinical group must be performed within 2 weeks after the baseline evaluation (T1). Patients in the control arm will continue to receive a weekly reading therapy session, as per common practice in France [15]. To control for potential bias related to the formation of speech and reading therapists, years of graduation and the training courses followed in the last 5 years will be recorded.

A second evaluation (T2) will take place via videoconference 12 weeks (+ or - 14 days) after the first day of training with Poppins Clinical for the experimental arm, or 12 weeks after the baseline evaluation for the control arm. Questionnaires for patients, their legal guardians, and speech and reading therapists will be collected at this time. Please refer to Figure 1 for a flowchart of the study procedures.

Throughout the trial, investigators and evaluators will remain blinded to the patients’ group assignments. However, patients and their speech and reading therapists will not be blinded to the allocation. To maintain blinding of the investigators and evaluators, the CRO’s safety department will be responsible for recording all adverse events and device deficiencies.

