### Outcomes

The primary outcome of this study is reading accuracy, which will be measured by the number of correctly read words using the EVALEO (Ortho Edition) [37] 2-minute word reading test (EVAL2M). Noninferiority will be evaluated 12 weeks after the start of training with Poppins Clinical for the experimental group or 12 weeks after the baseline evaluation for the control group.

Safety will be assessed by monitoring adverse events reported by patients during the 12-week study duration.

Seven secondary outcomes will also be investigated. Noninferiority in reading speed, measured by the number of words read using the EVAL2M [37], will also be evaluated. In addition, noninferiority in word reading skills (speed and accuracy) and meta-phonological skills will be assessed using respectively the Alouette-R [38] text reading test and the BALE Phoneme Suppression Test [39].

The impact of Poppins Clinical on parents’ stress levels and quality of life will be measured using the Parenting Stress Index-Short Form (PSI-SF) and the EQ-5D-5L [40] quality of life questionnaire. Text comprehension will also be assessed through the computerized BMT-i test battery [41], evaluating correct answers to comprehension questions, as well as reading precision and speed. A cost evaluation will be conducted by administering a questionnaire to parents to evaluate the health and economic value of Poppins Clinical. The objective is to determine in each group the direct and indirect health care costs, including, treatment costs (eg, number of appointments and costs of each session) and work-related costs (eg, the number of days off used for health purposes).

A total of 5 exploratory end points will be investigated. The effect of Poppins Clinical on visual attention span will be assessed with the EVALEO test, using correct answer scores. The patient’s quality of life and reading and writing difficulties will be evaluated using the PedsQL 4.0 CORE [42] young child report and a self-assessment grid for reading and writing difficulties [43]. The perceptions of parents and speech therapists regarding the study’s impact on therapy will be captured via an adapted questionnaire. Finally, predictive factors of training effectiveness with Poppins Clinical will be explored to improve the individualization of the program and the use of the device through connection data.

All the outcomes are described in Table 1.

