All outcomes will be evaluated 12 weeks after the start of training for the experimental group or 12 weeks after the baseline evaluation for the control group. Participants of the experimental group will have up to 14 calendar days to start training with Poppins Clinical once the baseline evaluation is completed. The results will be entered into an electronic case report form (eCRF) hosted on the web by the CRO, which will be responsible for data monitoring and treatment.

**Table 1 table1:** Measured outcomes investigated in the protocol.

Outcome	Measure
Primary outcome	Reading accuracy is measured by the number of correctly read words (EVAL2M)
Safety secondary outcome	Number of adverse events reported during the study
Secondary outcome 1	Reading speed is measured by the number of read words (EVAL2M)
Secondary outcome 2	Word reading accuracy and speed (Alouette-R)
Secondary outcome 3	Cost evaluation
Secondary outcome 4	Phoneme suppression skills (BALE)
Secondary outcome 5	Parental stress levels measured using the Parenting Stress Index Short Form
Secondary outcome 6	Parent’s quality of life measured using the EQ-5D-5L
Secondary outcome 7	Reading precision, speed, and comprehension (BMT-i)
Exploratory outcome 1	Visual attention span (EVALEO)
Exploratory outcome 2	Child’s quality of life (PedsQL 4.0 CORE)
Exploratory outcome 3	Child’s perception of reading and writing difficulties [43]
Exploratory outcome 4	Perception of parents and speech therapists on the impact of the protocol on the child (custom questionnaire)
Exploratory outcome 5	Evaluation of predictive factors of training effectiveness

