### Statistical Justification of the Sample Size

The sample size determination was based on the primary end point, which is to demonstrate the noninferiority of a follow-up with reading therapy every 2 weeks, in addition to the use of the digital medical device (Poppins Clinical), compared with a follow-up with reading therapy every week, on the evolution of reading accuracy over 12 weeks. The null (H0) and alternative (H1) hypotheses for noninferiority trials may take the following form:

H0: experimental (EXPE) is inferior in terms of the mean response, μEXPE–μCONT≤−ΔNI.H1: experimental is noninferior in terms of the mean response, μEXPE−μCONT>−ΔNI.

Where μEXPE is the mean of the outcome in the experimental arm, and μCONT is the mean of the outcome in the control arm. The noninferiority limit, –ΔNI, is defined as the threshold at which the mean difference between the experimental arm and the control arm becomes clinically unacceptable.

The noninferiority margin was determined through a formal expert committee meeting, combining independent experts and investigators. The committee was structured to ensure both independence and relevant expertise. Two independent experts were selected for their complementary expertise: a neuropediatrician who pioneered diagnostic recommendations for learning disorders in France, and a speech therapist who codeveloped the standardized assessment tool used as the primary outcome in this study (EVALEO 6-15). The two investigators of the study, both professors in child psychiatry with extensive research experience in neurodevelopmental disorders, provided their methodological expertise. A fifth expert, a neuropsychologist with experience in written language rehabilitation guidelines and as a reviewer of good practice recommendations, was included as a scientific advisor. All experts were active clinicians and researchers in learning disabilities.

The committee’s decision was informed by empirical data from the previous randomized controlled trial (ML-01), showing a natural progression of 7.7 (SD 12.9) correctly read words over 8 weeks in the placebo group [26]. Based on these data and their collective clinical experience, they established that a difference of 5 words or fewer between groups would represent a clinically acceptable margin of noninferiority. This threshold was unanimously approved by the full committee after a structured discussion of potential age-related variations in reading progression.

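### T2 is timed from first game use in the experimental arm but from baseline in the control arm, so the start delay (up to 2 weeks) biases the primary comparison toward noninferiority

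*Protocol article*

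**What the plan says.** Study Procedure in the Protocol article places T2 "12 weeks (+ or - 14 days) after the first day of training with Poppins Clinical for the experimental arm". The same sentence gives controls a different starting point: "12 weeks after the baseline evaluation for the control arm". Outcomes repeats the two starting points for the primary endpoint: "12 weeks after the start of training with Poppins Clinical for the experimental group or 12 weeks after the baseline evaluation for the control group". It also allows a gap before the experimental clock starts: "Participants of the experimental group will have up to 14 calendar days to start training with Poppins Clinical once the baseline evaluation is completed". Study Procedure gives the same two-week limit.

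Baseline is T1 in both arms, and randomization follows it. The sample size section describes the target as a comparison "on the evolution of reading accuracy over 12 weeks", and reports from the earlier placebo-controlled trial a "natural progression of 7.7 (SD 12.9) correctly read words over 8 weeks" in the placebo group.

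Criteria Analysis requires noninferiority in both ITT and PP, and keeps late assessments in ITT. Nothing in the article equalizes the T1-T2 interval between arms or adjusts for it.

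**The concern.** The primary comparison concerns progress from T1, but time from T1 to T2 is not the same by design. Control children are tested a nominal 84 days after T1. Experimental children are tested 84 days after first use, which can itself come up to 14 days after T1. Some delay is to be expected, because the family must create an account through a study link after randomization. Nothing moves the control clock to match.

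Schooling, maturation and any therapy in that gap raise the experimental arm's T2 score and are credited to the experimental strategy. In a noninferiority trial this is the unsafe direction, since it hides part of a true deficit. ITT does not help, because the schedule creates the difference. PP does not help either, because it uses the same T2 dates. The follow-on superiority test and the other T2 outcomes carry the same offset.

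**Working it through.** **Inputs** (Statistical Justification of the Sample Size, unless noted)
- Margin 5 words; SD 12.7; one-sided alpha 2.5%; power 90%; 137 per group; 10% dropout; 306 in total.
- Placebo-group gain: 7.7 words in 8 weeks.
- Start delay: 0 to 14 days (Study Procedure; Outcomes).
- Assumed, because the documents do not say: the mean start delay, and that the gain is linear and carries on to weeks 12 to 14.

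**Plan's own figure.** With a true difference of 0, the normal approximation gives 136 per group. The noncentral t calculation gives 137, with power 0.901. Then 137/0.90 = 152.2, rounded up to 153 per arm, or 306. The stated size is reproduced, and it assumes no timing difference between arms.

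**Intervals from T1 to T2**
- Control: 84 days.
- Experimental, nominal: 0 + 84 = 84 to 14 + 84 = 98 days, that is 12 to 14 weeks.

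**Rate of gain.** 7.7/8 = 0.9625 words per week. Some of the 7.7 words may be retest gain, which does not grow with a longer interval, so half the rate (0.481) is shown as well.

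**Bias and type I error**
- SE = 12.7 × √(2/137) = 1.534.
- Bias = mean delay in weeks × weekly rate.
- Type I error at a true difference of -5 words = Φ(bias/SE − 1.96).

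| Mean start delay | Words per week | Bias (words) | Share of margin | Type I error |
|---|---|---|---|---|
| 0 | any | 0 | 0% | 2.5% |
| 3 days | 0.9625 | 0.41 | 8% | 4.5% |
| 1 week | 0.481 | 0.48 | 10% | 5.0% |
| 1 week | 0.9625 | 0.96 | 19% | 9.1% |
| 2 weeks (limit) | 0.481 | 0.96 | 19% | 9.1% |
| 2 weeks (limit) | 0.9625 | 1.93 | 38.5% | 24.0% |

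Example, 1 week at full rate: 0.9625/1.534 = 0.627; 0.627 − 1.96 = −1.333; Φ(−1.333) = 0.091.

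With a common starting point and window the bias is 0, the error rate returns to 2.5%, and 137 per group is unchanged.

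**The case against.** Timing T2 from first use has a clear purpose: it gives every child who starts the planned 12 weeks of play. Controls simply continue weekly therapy, so they have no start date to wait for. The choice trades equal elapsed time for equal exposure. That explains the rule, but it does not remove the bias, because the primary comparison is of progress from T1.

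The size is uncertain, and this objection stands in full. The 24% needs every child to start on the last permitted day and to progress at the full placebo rate. With short delays the inflation is slight.

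A reader might infer stronger points that the document does not support:
- *Experimental children get up to 4 extra weeks, worth 3.85 words or 77% of the margin.* That is one child who starts on day 14 and is tested 14 days late (14 + 84 + 14 = 112 days). It is not an arm average. The window is written only beside the experimental arm, but it is two-sided and adds no systematic bias if used symmetrically. The sentence does not exclude that it covers controls too.
- *The bias favours the experimental arm in every case.* A child who starts on day 0 and is tested 14 days early has 70 days, fewer than a control's 84. The direction holds for the arm average, through the start delay.
- *Children who never start have no T2 date.* A visit rule for them is operational detail that an article may leave to the full protocol.
- *The longer interval unblinds evaluators.* Nothing says that evaluators see the start date or the interval, and the experimental range of 70 to 112 days includes 84.

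A change also comes late. Recruitment was expected from December 2024 and completion by the end of August 2025, so an amendment could leave two T2 rules in one trial.

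**Conclusion.** The unequal starting points are certain: the article states them in Study Procedure and repeats them in Outcomes. On average they lengthen the experimental arm's T1-T2 interval by the mean start delay, somewhere between 0 and 2 weeks, and push the primary result toward noninferiority in both ITT and PP.

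The size depends on delays that are not reported. It runs from about 0.4 words and a 4.5% error rate (3-day mean delay, full rate) to 1.93 words and 24% (2-week limit, full rate). A 1-week mean delay gives about 5 to 9%. These figures rest on a true deficit of exactly 5 words, an SE of 1.53, linear progress, and a rate borrowed from an 8-week placebo group. The finding rests on the start delay alone, not on the ±14-day window.

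**What to change.** Schedule T2 at the same number of weeks after T1 (or randomization) in both arms, for all randomized children, and state one window that applies to both.

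For children already assessed under the current rule, add a prespecified sensitivity analysis of the primary endpoint. From each T2 score, subtract (T1-T2 days − 84) × the control arm's observed daily gain, and compare the arms again against the 5-word margin. The observed gain includes any retest effect, so a second run at half that rate would show how much the result depends on it. This analysis supports a common starting point but does not replace it. Reporting the distribution of start delays and T1-T2 intervals by arm would settle how large the bias was.

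**Cost.** A protocol amendment and a change to visit scheduling, with no extra visits and no change to the 306 participants. If T2 stays at T1 + 12 weeks, late starters have slightly less game time when tested. If a later common time such as T1 + 14 weeks is chosen, T2 falls up to 2 weeks later for controls and early starters, and the 12-week endpoint wording must be amended.
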